**Multiple comparisons and multiplicity**

Results from all analyses will be assessed against an alpha of 0.05. There will be no adjustments for multiplicity as there are pre-defined outcomes and objectives, and the influence of individual results on the overall interpretation of the study will reflect their importance.

**Covariate adjustment**: The primary statistical analyses for the outcome variables “APO” measured at the follow-up visit will be adjusted by performing analyses adjusted for other baseline characteristics suspected *a priori* to be associated with the outcome. Any group differences in potentially influential baseline characteristics will be included in the interpretation and discussion of results.

**Incomplete follow-up:** For each subject, participation in the study will end at birth/pregnancy outcomes. If a subject migrates or withdraws, data collected until that point in time will be used.

**Missing outcome data:** All precautions should be made for no missing values on baseline variables that are planned for use as covariates. For the primary outcome and secondary outcomes, subject who do not have a measurement taken at the baseline or subsequent follow-up visit will be restricted from the final analysis.

**Outliers:** Outliers will be identified by examining residual plots. Cases that visually “stand out” will be assessed for a possible influence on results. A comparison of results from analyses with and without the outlier(s) may be performed. Where there are discrepant results from the two analyses, this will be reported and discussed in the manuscript(s).

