**Study Outcome Measures**

**A) Primary:** The primary outcome of interest will be the incidence of an adverse pregnancy outcome (APO), defined as an event of either preterm birth (PTB), low birth weight (LBW), or both, spontaneous abortion, and still birth. We will use World Health Organization (WHO) definitions for all primary outcome measures. Preterm birth will be defined as birth of a live baby before 37 completed weeks of gestation or fewer than 259 days since the first day of the woman’s last menstrual period. Neonates weighing < 2500 grams at birth will be considered to be of LBW. Spontaneous abortion will be defined as “fetal loss” before 22 weeks of gestation with gestational age estimated from the participants’ self-reported last menstrual period. Stillbirth will be defined as fetal death after 22 weeks gestation with no sign of life (cord pulsation or muscle movement). Infant demographics such as gestational age, birth weight, and gender of the child should be abstracted from medical charts at delivery by the CHV. The birth data should be recorded into a customized mother-baby tracking cards provided to all pregnant women for future follow-up purposes.

Infant demographics such as gestational age, birth weight, and gender of the child will be abstracted from the birth records by the CHV at the delivery and should be entered individual mother-baby cards. For interpretation purposes we will classify the outcomes into three categories (APO, PTB and LBW). All reported adverse pregnancy outcomes (PTB, LBW, stillbirth and abortions) will be grouped into one category and will be referred as “adverse pregnancy outcomes (APO)”; PTB and LBW may be interpreted separately.

**B) Secondary:** We anticipate studying the following secondary outcomes using the same cohort:

1) Incidence of change of sanitation behaviour

2) Incidence of UTI/BV symptoms

3) Prevalence of anaemia and BMI status among the pregnant cohort

4) Incidence of morbidities such as malaria, gastrointestinal illness etc.

5) Key social, cultural, and economic considerations that serve as motivators and barriers among pregnant cohortto adopt improved sanitation and hygiene practices

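### The SAP's two rules for incomplete data are not reconciled, and exclusion depends on a visit measurement instead of on whether the pregnancy outcome is known

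*SAP*

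**What the plan says.** Both rules stand in the SAP under Multiple comparisons and multiplicity.

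- **Incomplete follow-up:** "For each subject, participation in the study will end at birth/pregnancy outcomes". Then: "If a subject migrates or withdraws, data collected until that point in time will be used".
- **Missing outcome data:** the scope is set by "For the primary outcome and secondary outcomes, subject who do not have a measurement", and the consequence is that a "subject who do not have a measurement taken at the baseline or subsequent follow-up visit will be restricted from the final analysis".

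Three other places bear on how to read them. Study Outcome Measures puts fetal losses in the primary outcome: "All reported adverse pregnancy outcomes (PTB, LBW, stillbirth and abortions) will be grouped into one category". The Covariate adjustment paragraph describes APO as "measured at the follow-up visit". Quality Control and Quality Assurance has a supervisor return to the household to confirm each outcome of interest that is reported. Women enter at 10-12 weeks of gestation (Statistical Analysis Plan section).

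**The concern.** The two rules give different answers for the same woman. If she withdraws after recruitment and before a later visit, one paragraph uses her data and the next takes her out of the final analysis of every outcome.

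For APO there is a second difficulty. The exclusion is triggered by a missing visit measurement, whereas the question that matters is whether the pregnancy outcome is known. Follow-up stops at the pregnancy outcome, so an early loss leaves little time for a later visit. A woman who delivers preterm but has no recorded birth weight, or who missed an antenatal visit, is in a similar position: her APO status is established, yet a measurement is missing. If such women are dropped, entry to the primary analysis depends partly on the outcome. The risk ratio may then shift as well as lose precision.

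**Working it through.** **1. The rules applied to four cases**

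| Woman | Incomplete follow-up rule | Missing outcome data rule | APO status |
|---|---|---|---|
| Migrates before any later visit | data used | excluded, all outcomes | unknown |
| Attends some visits, then withdraws | data used | unclear which visit counts | unknown |
| Miscarries before any later scheduled visit | participation complete | excluded if a scheduled visit is meant; kept if ascertaining the outcome counts as the measurement | known: APO |
| Preterm live birth, birth weight missing | participation complete | unclear which measurement is required | known: APO |

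Row 1 is the direct conflict. It matters most for secondary outcomes such as urinary tract infection or bacterial vaginosis symptoms, other morbidities and change of sanitation behaviour. Rows 3 and 4 are the ambiguity for the primary outcome.

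**2. The plan's own figures.** Inputs from Sample Size and Power of the Study: P0 = 0.20, P1 = 0.30, ratio 1:1, two-sided alpha 0.05, power 80%, 15% dropout, 670 enrolled.

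- Unpooled variance: n per group = (0.16 + 0.21) × (1.96 + 0.84)² / 0.10² = 290.1, rounded up to 291, so 582 in total. This matches the SAP. The pooled formula without continuity correction gives 588.
- After 15% loss: 670 × 0.85 = 569.5 women, about 285 per group, with power 79% for 20% vs 30%.

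**3. Illustration: known losses dropped.** The SAP gives no fetal-loss rate, so L0 and L1 (losses as a share of pregnancies, unexposed and exposed) are assumptions. If all losses are dropped:

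analysed RR = [(P1 − L1)/(1 − L1)] / [(P0 − L0)/(1 − L0)]

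Power uses the pooled two-proportion formula, starting from 285 per group before the losses are removed.

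| L0 | L1 | Analysed risks | RR | Power |
|---|---|---|---|---|
| none dropped | none dropped | 0.200 vs 0.300 | 1.50 | 79% |
| 4% | 8% | 0.16/0.96 = 0.167 vs 0.22/0.92 = 0.239 | 1.44 (1.435) | 55% |
| 4% | 8%, half dropped | 0.18/0.98 = 0.184 vs 0.26/0.96 = 0.271 | 1.47 | 69% |
| 4% | 6% | 0.167 vs 0.24/0.94 = 0.255 | 1.53 | 72% |
| 4% | 4% | 0.167 vs 0.26/0.96 = 0.271 | 1.63 (1.625) | 84% |

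With L0 = 4%, the analysed RR stays at 1.50 when (0.30 − L1)/(1 − L1) = 1.5 × 0.1667 = 0.25. That gives L1 = 0.05/0.75 = 6.7%. Above this the RR moves towards 1, below it away from 1. A more extreme assumption, losses making up 10% of APO in the unexposed (2% of pregnancies) and 40% in the exposed (12%), gives (0.18/0.88)/(0.18/0.98) = 1.11.

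**4. Illustration: outcome truly unknown.** Suppose a fraction m of a group is missing and carries k times the risk of those observed. The observed risk is P/(1 − m + k·m). With m = 10% unexposed and 20% exposed:

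- k = 1.5: 0.20/1.05 = 0.190 and 0.30/1.10 = 0.273, RR 1.43.
- k = 2: 0.20/1.10 = 0.182 and 0.30/1.20 = 0.250, RR 1.38 (1.375).

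These m and k are also assumptions.

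**The case against.** The strongest reply is that no sentence in the SAP excludes abortions or stillbirths. They are named in the primary outcome, APO is described as measured at follow-up, and a supervisor confirms each reported outcome at the household. The exclusion sits under a heading about missing outcome data, so it can be read as applying only to women whose outcome was never obtained. On that reading an ascertained abortion is itself the measurement and the woman stays in. This stands as a possible reading. It does not settle the matter, because the sentence speaks of a baseline or later visit and leaves the visit undefined.

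It can also be said that the two rules are compatible for APO: a woman lost before delivery has no APO value, and her earlier data can still serve descriptive and visit-based analyses. That is sensible, but the SAP does not say it, and the exclusion expressly covers secondary outcomes too.

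A reader might infer that births without a medical chart are removed as well, since infant data "should be abstracted from medical charts at delivery by the CHV". The document does not support this: the rule speaks of a measurement and not of a chart, the same section also names birth records, and no figure on missing charts or their link to exposure is given.

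Finally, a complete-case model is not biased merely because women are lost. If missingness depends only on exposure and the planned covariates, a correctly specified adjusted model remains consistent. Weighting or imputation on nearly the same variables would then add little, and would not cure the excess-risk situation in step 4. That argues for using these methods as sensitivity analyses and not as the primary analysis.

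**Conclusion.** The concern holds in this form: the SAP states two rules that are not reconciled, most plainly for visit-based secondary outcomes, and its exclusion rule for APO is keyed to a visit measurement in a way that could, read literally, delete women whose APO status is established.

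A reader might go further and conclude that the SAP removes pregnancies because of their outcome, or that the risk ratio will be biased towards 1. Neither is supported. The first is the consequence of one reading. The second depends on loss rates the SAP does not give: under true risks of 20% and 30%, the illustrations run from RR 1.11 to 1.63, on both sides of 1.50. What can be said is that the rule decides who enters the primary analysis, that one plausible reading removes primary-outcome events, and that the benign case cannot be assumed, because an effect of sanitation on fetal loss is part of what the study sets out to examine.

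**What to change.** Replace the exclusion sentence, before analysis, with text that does the following.

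1. Every enrolled woman with a known pregnancy outcome enters the APO analysis, whatever visits were missed.
2. APO is present once any component (abortion, stillbirth, preterm birth or low birth weight) is established, even if another component is missing. APO is absent only when all components are ruled out. A term live birth with no birth weight is therefore unknown, not a non-case.
3. Only women with an unknown outcome are left out of the APO model. Their data up to loss are used for descriptive and visit-based secondary analyses. Align the Incomplete follow-up sentence with this.
4. Loss is reported by exposure group.
5. For unknown outcomes, add a sensitivity analysis: inverse-probability weighting or multiple imputation on exposure and the baseline covariates (site, age, BMI, haemoglobin, poverty, education), plus a missing-not-at-random scenario of the kind in step 4 of the working.

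The cost is SAP wording and modest extra analysis, with no new data collection. The weighting or imputation relies on a missing-at-random assumption, which is why it belongs beside the main analysis and is paired with a scenario that relaxes it.

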**Data management and analysis software**

Database will be created using Epi-Info custom-designed database management interface. Most data manipulation, tables, figures, listings and analyses will be documented in Stata programs and performed using Stata® Software version 13.

**Data confidentiality**

All the collected data from the participants of the study will be in line with the Health Insurance Portability and Accountability Act of 1996 (HIPAA). HIPAA establishes security and privacy standards for the use and disclosure of “protected health information” (PHI) of study participants. Only de-identified data will be used for further analysis.

**Quality Control and Quality Assurance**

Quality of data collected by CHVs will be ensured through direct supervision and random checking by respective field supervisors, and further checking of a subset by the project manager. Supervisory visits and standardization exercise sessions will be organized routinely to ensure quality of data collection. Every reported outcome of interest will be confirmed by a repeat visit to the household by a supervisory staff. A sample (10%) of collected forms will be cross-checked by the supervisory team. Data will be double entered to a custom-designed database management interface using Epi-Info. Some data points will be randomly selected for comparison between the paper report and the electronic database. Field verifications will be conducted to resolve identified inconsistencies and incompleteness as and when required.
